**Methods:**

In this single-blinded, randomized, controlled, parallel-group superiority trial with 1:1 allocation ratio, 164 patients with OUD availing the outpatient/ inpatient clinical services at a tertiary mental healthcare hospital in India will be enrolled after giving informed consent. Consecutive consenting patients will be randomly allotted to one of the two groups − yoga arm (standard treatment + yoga-based intervention), or waitlist group (standard treatment alone). Allocation concealment will be followed, the clinicians, outcome assessors and data analysts will remain blind to subject-group allocation. A validated and standardized yoga program for OUD will be used as an intervention. Participants in the yoga arm will receive 10 supervised in-person sessions of yoga in the initial two weeks followed by tele-yoga sessions thrice a week for the next 22 weeks. The wait-list control group will continue the standard treatment alone for 24 weeks. Assessments will be done at baseline, two weeks, 12 weeks, and 24 weeks. Data from all randomized subjects will be analysed using intent-to-treat analysis and mixed model multivariate analysis.

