### Clinical assessment

The demographic and clinical information will be collected using structured scales and proforma. Diagnosis of OUD will be made as per Diagnostic and Statistical Manual of Mental Disorders (DSM 5) criteria and participants will be screened using Diagnostic Interview for Anxiety, Mood, and OCD and Related Neuropsychiatric Disorders (DIAMOND)^54^. The clinical diagnosis would also be confirmed independently by a qualified psychiatrist. Pain and Craving will be assessed by Brief Pain Inventory (BPI) and Opioid Craving Scale (OCS), respectively. Withdrawal symptoms will be assessed by Clinical Opiate Withdrawal Scale (COWS). The Time-Line Follow Back (TLFB) method will be employed at the three- and six-month intervals to quantify self-reported frequency of opioid use and maximum weeks of abstinence. The TLFB is a reliable and valid tool in assessing self-reported drug use and leverages a calendar and significant events to aid participants in recalling their substance use patterns, thereby offering a comprehensive view of consumption trends over time^55^. Perceived stress will be assessed using the perceived stress scale (PSS). Work and social life will be rated on the Work and Social Adjustment Scale (WSAS) and Quality of Sleep on Pittsburg Quality of Sleep Index (PSQI). Adverse effects of opioid substitution therapy (buprenorphine/naloxone) will be assessed using the Udvalg for Kliniske Undersogelser (UKU) Side Effects Rating Scale.

In addition, traditional diagnoses related to yoga therapy will be determined at baseline using the Vedic Personality Inventory and Ayu-Soft Prakriti Diagnostic Tool. Table 1 provides the schedule of assessment.

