### Data analysis

The R programming language will be used to analyze data (R Core Team 2022; 56). Details of dropped-out/withdrawn patients will be recorded. Missing data, drop-outs, non-compliance, and adverse events will be managed in collaboration with the biostatistician and supervisor. The data of all randomized participants will be analyzed using intent-to-treat analysis and mixed model multivariate analysis. Imaging analysis details are provided below. OST/MOUD dosage will be used as a covariate in the analysis. Interim analysis will be done when 50% of the target sample size completes the trial. Information regarding solicited and spontaneously reported adverse events and other unintended effects of trial interventions or trial conduct will be documented and reported to the DMC as well as the ethics committee of the institution. The DMC will have access to interim analysis results and will take the decision to terminate the trial in case of unreasonable morbidities or mortalities among the recruited participants during the trial. Information obtained from the interim analysis may be used for enhancing trial efficiency by updating design and/or sample size adjustments, this will be done as per the suggestions of DMC and after due approval from the funding agency. Trial conduct will be audited once in a year by the DMC, the process will be independent from investigators and the sponsor.

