### Intervention

#### Yoga-add on therapy (YAT: Standard treatment + yoga)

Based on our previous clinical experience the duration of intervention was decided to be 24 weeks^48–51^. Yoga will be offered as an add-on to standard treatment. Participants will be trained in a 40-minute validated yoga module (30 minutes practice+10 minutes relaxation)^48^ during the withdrawal phase and a 60-minute yoga module (45 minutes practice+15 minutes relaxation) during maintenance phase by a trained yoga-instructor (MSc Yoga Science) at the Department of Integrative Medicine, NIMHANS Bengaluru. Table 2 and Table 3 provide the details of the yoga practices to be used during withdrawal and maintenance phase, respectively. Initial supervised training will be conducted for two weeks (five sessions/week). Participants will be asked to join supervised tele-yoga practice from home for the next 22 weeks (at least three days/week). A monthly direct supervised booster session along with yoga-practice booklet, logbook and practice video will be provided. A mobile phone software application will be used to share yoga videos with the participants. Yoga compliance and fidelity to the yoga module (when it has to be done by oneself using video) will also be assessed. Patients will also be monitored by phone calls. Yoga performance will be monitored through the yoga performance assessment scale (YPA).

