#### Standard treatment-as-usual (TAU waitlist) group

They will continue to take prescribed medications (OST/MOUD) and psychosocial support as prescribed by the psychiatrist. They will be requested to appear for the planned assessments and will be offered yoga after the six-month study period.

The allocated intervention may be discontinued or modified in case of any subject reporting worsening of symptoms. This data will be documented.

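### Spontaneous adverse-event reports may be captured more fully in the yoga arm, because it has about 81 extra scheduled staff contacts and no general event checklist is common to both arms

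*Protocol article*

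**What the plan says.** **Safety data.** The protocol article, Data analysis, states: "Information regarding solicited and spontaneously reported adverse events and other unintended effects of trial interventions or trial conduct will be documented". The same sentence sends this information to the DMC and the institution's ethics committee. The section also lets the DMC end the trial if morbidity or mortality among participants is judged unreasonable.

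**Yoga arm.** The intervention section gives three kinds of scheduled session:
- "Initial supervised training will be conducted for two weeks (five sessions/week"; the abstract agrees: "Participants in the yoga arm will receive 10 supervised in-person sessions of yoga in the initial two weeks".
- "Participants will be asked to join supervised tele-yoga practice from home for the next 22 weeks (at least three days/week".
- Boosters under direct supervision, once a month; their total is not stated.

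It adds: "Patients will also be monitored by phone calls". That sentence appears only in the yoga-arm description, and no number of calls is given.

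**Control arm.** Besides prescribed medication and psychosocial support, the section on the waitlist group says: "They will be requested to appear for the planned assessments and will be offered yoga after the six-month study period".

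**Common to both arms.** Table 1 has four visits (day 0, 15 days, three months, six months), and its urine row is marked monthly. Study setting says that routine standard care continues for everyone. The UKU is scheduled at all four visits. Clinical assessment describes its purpose: "Adverse effects of opioid substitution therapy (buprenorphine/naloxone) will be assessed using the Udvalg for Kliniske Undersogelser (UKU) Side Effects Rating Scale".

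**The concern.** A spontaneous report needs an occasion on which to make it. The plan counts such reports among its safety data, while scheduling many more occasions in one arm than in the other. The extra occasions are with yoga staff. They necessarily know the allocation and are not among those whom Study setting lists as blinded (treating clinicians, outcome assessors, data analysts).

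If an event is a buprenorphine/naloxone side effect, the UKU asks about it equally in both arms. For an injury, overdose, hospital visit or act of self-harm, no item in Table 1 is described as asking. Such an event would reach the file through a volunteered report or through routine care.

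Two consequences could follow:
- Minor complaints raised during sessions could make yoga look less safe than it is.
- Events in controls could go unrecorded. The Background itself names overdose and suicide as causes of death in this disorder.

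The second cannot be mended at the analysis stage. A later analysis plan can separate events by source, but it cannot recover control events that nobody asked about.

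**Working it through.** **1. The plan's own figure.** The only session total that the article states is 10 in-person sessions (abstract). The intervention section gives 2 weeks × 5 per week = 10, which agrees.

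**2. Extra scheduled contacts, yoga arm.**
- In person: 2 × 5 = 10.
- Tele-yoga: 22 weeks × at least 3 per week = at least 66.
- Boosters: monthly, count not stated; 5 to 6 assumed.
- Total: 10 + 66 + 5 = 81, or 82 with 6 boosters, before phone calls.
- If only half the tele-yoga sessions are attended (assumption): 10 + 33 + 5 = 48.

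**3. Extra scheduled contacts, control arm.** None is described. This refers to extra contacts only.

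**4. Contacts shared by both arms after baseline.** There are three visits (15 days, three months, six months). If the monthly urine test brings participants in at months 1, 2, 4 and 5 as well, there are 3 + 4 = 7. Routine psychiatric care comes on top, at a frequency that is not stated.

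**5. What is asked equally.** The UKU is asked at the same four time points in both arms, so solicited medication side effects are unaffected by the imbalance. The exposed part is everything outside its described scope.

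**6. Possible size.** The documents give neither an event rate nor a detection probability, so the bias cannot be computed. An illustration uses

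observed risk = true risk × probability that an event is recorded.

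With equal true risk, the apparent risk ratio is (detection with yoga) / (detection in controls). Assumptions: 90% detection with yoga, true risk 20%, and 82 per arm (from Sample size estimation). Expected participants with a recorded event in the yoga arm: 82 × 0.20 × 0.90 = 14.8.

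| Control detection (assumed) | Apparent risk ratio | Control participants with a recorded event |
|---|---|---|
| 50% | 0.90 / 0.50 = 1.80 | 82 × 0.20 × 0.50 = 8.2 |
| 70% | 0.90 / 0.70 = 1.29 | 82 × 0.20 × 0.70 = 11.5 |
| 90% | 0.90 / 0.90 = 1.00 | 82 × 0.20 × 0.90 = 14.8 |

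The ratio does not depend on the assumed true risk; the counts do. If routine care picks up control events as well as the sessions pick up yoga events, there is no distortion.

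**The case against.** The strongest reply is that the article nowhere says adverse events are collected at yoga sessions. Data analysis names no collector, form or occasion. It lists solicited and spontaneous events as two kinds without saying that they are merged, and it describes no between-arm safety table. The DMC's criterion concerns morbidity and mortality among participants generally, and deaths and serious morbidity probably depend least on how often someone is seen. Event forms and safety-table layouts commonly sit in a full protocol or analysis plan that is not shown. Unequal contact is also inherent in testing a session-based intervention against a waitlist.

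Much of this stands, and it rules out several stronger readings that a reader might infer:
- *A safety comparison sent to the DMC is biased against yoga.* No such comparison is described, and the route through yoga contacts is an inference. Only possible bias in recorded counts can be claimed.
- *Controls have no contact.* They share the assessments, the monthly urine tests and continuing psychiatric care.
- *Yoga participants are asked about their health many times as often.* Dividing contacts gives (81 + 3) / 3 = 28, or (81 + 7) / 7 = 12.6. These ratios count sessions, not health questions. They assume full attendance, although the article expects 36% drop-out, and they leave out routine care. Turning them into event percentages would need per-contact reporting probabilities that the documents do not give.

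What the reply does not remove is the combination that the article does state: spontaneous reports belong to the safety data, one arm has a far denser contact schedule, and the one common side-effect scale is tied to medication. The point therefore does not rest on a missing form.

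**Conclusion.** The point holds in a limited form. As written, the plan makes the capture of events other than buprenorphine/naloxone side effects depend partly on arm. The likely direction is more recorded events with yoga and under-recording in controls. The contact imbalance is firm: about 81 extra scheduled contacts at full attendance (five boosters assumed), or about 48 at half tele-yoga attendance, against none described for controls. The effect on event counts is not known. The range of 1.00 to 1.80 for the apparent risk ratio is an illustration under assumed detection probabilities and equal true risk, not an estimate. UKU data are not affected. The documents do not support a claim that harms results will be uninterpretable or that the DMC will be misled. The point merits action because the remedy is cheap and works only if it is in place while data are being collected.

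**What to change.** **Change.**
- Ask one short, neutrally worded adverse-event checklist (any new injury or symptom, overdose, hospital visit, self-harm) of both arms at the existing common visits: 15 days, three months, six months and each monthly urine collection. Recall should run back to the last common contact.
- State that any between-arm comparison of harms rests on those answers plus the UKU.
- Report every other event in full to the DMC and the ethics committee, including those raised at yoga sessions or by phone. Tabulate these by source and discard none. An injury sustained during yoga would normally be picked up again at the next common visit; if it is not, it is still reported.

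**Cost.** One short form, a few minutes per visit and a sentence in the plan; no visits are added. The comparison then relies partly on recall. Asking about injuries also carries a small risk that a participant discloses the allocation to the blinded assessor. Neutral wording that does not mention yoga limits this but does not remove it.

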### Sample size estimation

For evaluating the primary objectives, the optimal sample size was estimated using the principles and methods for the assessment of primary parameters (abstinence, pain, craving, plasma beta-endorphins and fMRI changes). Based on approximation and estimation from the previous data on the clinical effects of yoga interventions in OUD/other patients with substance use disorder supporting a medium effect size^37,40,43,44^, it was estimated that, for an allocation ratio of one, a sample size of at least 82 OUD patients in each arm (accounting for a potential drop-out rate of 36% at six months^40^ with 60 completing the entire study (for the pre- versus post- comparisons of patients) will be required to detect a two-tailed significant difference of α = 0.01 with an estimated 80% power.

The subset sample size of 50 for imaging studies (in each group − pre as well as post-brain scans) will be sufficient to perform random effect analysis for fMRI BOLD changes with multiple comparison correction using random field theory-based family-wise error correction to control for multiple comparison (http://www.fil.ion.ucl.ac.uk/spm/).

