### Study setting

Patients with OUD availing the outpatient/inpatient clinical services under the Centre for Addiction Medicine, Department of Psychiatry, National Institute of Mental Health and Neuro-sciences (NIMHANS), Bengaluru, India will be approached. The course of the trial, its benefits, possible demerits, voluntary participation with a choice to quit the study at any time will be explained in simple comprehensible language. Patients satisfying the inclusion criteria will be requested to provide written informed consent. Consecutive consenting patients will be randomly assigned to one of the two groups − Standard treatment + Yoga-based intervention (YAT), or waitlist group-standard treatment (TAU) alone by the biostatistician. Allocation sequence will be generated by biostatistician using computer-generated random numbers and allocation concealment will be done using opaque sealed envelopes. A validated and standardized yoga program for OUD will be used as an intervention. Although double blinding will not be possible in the study, the clinicians treating the subjects, the outcome assessors, and data analysts will remain blind to the subject-group allocation status throughout the period of the study. All participants will be continuing their routine standard care (OST/MOUD and psycho-social support) till the study concludes. Figure 1 provides the study design outline.

Buprenorphine/naloxone dosage will be recorded at the beginning of yoga intervention; dosage will be adjusted based on the clinical presentation of the patient by the treating psychiatrist.

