### Data storage, handling, and statistical analysis

A data monitoring committee (DMC) will be created, which will be chaired by the biostatistician. The DMC will be independent from the sponsor and any competing interests. Data handling, coding and password-protected data storage will be supervised by a biostatistician. The biostatistician will also supervise data anonymization and data analysis. The data will be suitably anonymized so that no identification features are revealed. Data anonymization will be done by the biostatistician creating a mirror image of a database and implementing alteration strategies, such as character shuffling or encryption.

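### Interim results may reshape the trial with no stated protection of the 0.01 level, and the biostatistician's combined roles are in tension with the stated blinding and independence

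*Protocol article*

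**What the plan says.** **Adaptation.** The protocol's Data analysis section states: "Interim analysis will be done when 50% of the target sample size completes the trial". The DMC has access to the results. The only ground given for ending the trial is excess morbidity or mortality. The section then adds: "Information obtained from the interim analysis may be used for enhancing trial efficiency by updating design and/or sample size adjustments". Such changes follow the DMC's suggestions and need the funder's approval. The final analysis is described as intent-to-treat with mixed models. The level comes from Sample size estimation, where the planned number "will be required to detect a two-tailed significant difference of α = 0.01 with an estimated 80% power".

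**Roles.** Under Study setting: "Allocation sequence will be generated by biostatistician using computer-generated random numbers". The same paragraph has the biostatistician assign patients to groups. Under Data storage, handling, and statistical analysis: "A data monitoring committee (DMC) will be created, which will be chaired by the biostatistician", and also: "The biostatistician will also supervise data anonymization and data analysis". Under Data analysis, missing data and drop-outs are managed together with the biostatistician.

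**Assurances.** Study setting says that "data analysts will remain blind to the subject-group allocation status throughout the period of the study". The data storage section says the DMC is independent of the sponsor and free of competing interests. Data analysis says its yearly audit is independent of investigators and sponsor.

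**The concern.** There are two linked problems.

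First, the permission to adapt is open-ended. It covers design as well as sample size. It does not say whether pooled or between-arm results may drive the change, what may change, or within what limits. A conventional final test keeps its nominal level after a blinded re-estimation, essentially unchanged. It need not keep it after a change chosen in the light of the observed treatment difference. As worded, the protocol allows both.

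Second, the biostatistician made the allocation list, chairs the body that receives interim results and advises on redesign, and supervises the final analysis. If comparative interim results reach that role, they can influence the redesign, the handling of drop-outs and the choice of analysis. The DMC's audit would also cover work for which its own chair is responsible.

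**Working it through.** **Inputs.** Two-sided level 0.01 (Sample size estimation), so 0.005 per side and critical value c = 2.576. One interim (Data analysis). Two assumptions are needed because the protocol does not settle them: changes are driven by the between-arm result, and the final test is the ordinary unadjusted one. The interim information fraction t is also an assumption, and a range is shown.

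**Plan's own figure.** With no adaptation, the calculation below (n fixed at 1) returns 0.005 per side, or 0.010 two-sided, as stated. A re-estimation from pooled data leaves it at about 0.01.

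**Capped increase.** Let n be the final total as a multiple of the planned total, with n between 1 and 2. Given the interim statistic z1, the chance of crossing the upper bound at the end under no effect is

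1 − Φ[(c√n − z1√t) / √(n − t)].

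Take the n that maximises this at each z1, then average over the standard normal distribution of z1.

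| Information at interim | Per side | Two-sided |
|---|---|---|
| t = 0.50 | 0.0065 | 0.013 |
| t = 0.68 | 0.0070 | 0.014 |
| t = 0.78 | 0.0074 | 0.015 |

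The 0.78 takes 82 completers (half of 164) over 164 × 0.64 = 105 expected completers at 36% drop-out. The 0.68 takes 82 over 120, reading the protocol's 60 completers as per arm. Both treat completers as information. That is only approximate, because a mixed model also uses partial data.

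**Unlimited resizing.** The known bound per side is α + exp(−c²/2)/4 = 0.005 + 0.0362/4 = 0.005 + 0.0091 = 0.0141. Doubling gives 0.028. This is an upper limit, because no single resizing rule attains the worst case in both tails at once.

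**Changes of design other than size** (endpoints, arms, analysis) cannot be bounded from the text.

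**Roles against assurances.**

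| Biostatistician's task | Statement it is in tension with |
|---|---|
| Generates the sequence, assigns patients, supervises analysis | Data analysts blind throughout |
| Supervises analysis, helps manage drop-outs, chairs the DMC | DMC free of competing interests |
| Chairs the body that audits conduct, including this role's own work | Audit independent of investigators and sponsor |

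**The case against.** The strongest reply is that this is a condensed article. Adaptation rules, boundaries and error control usually sit in an analysis plan or DMC charter, and their absence here is no fault. The text does not say that the interim compares arms on efficacy, and it gives no efficacy stop, so the look by itself costs no alpha. Re-estimation from pooled data fits the wording and would leave the level essentially intact. Changes also need a DMC suggestion and the funder's approval.

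Most of this stands, and it limits the point. A reader might infer that the type I error is inflated. The documents do not show that, because they never say that between-arm results will be used or that the final test ignores the adaptation. A reader might also treat the interim as a second significance test, but none is described. What the reply does not remove is that the article itself grants the open permission. A later plan could repair this only by narrowing what the protocol allows. Approval by a funder is not error control.

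On roles, it can be said that supervising analysts does not unblind them, that nothing calls the biostatistician an investigator, and that the data storage section once uses the indefinite article, so two people may be meant. These are fair points, and they are why the finding is tension rather than proven contradiction. The other mentions nevertheless read as one role. If two people are intended, the protocol should say so.

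**Conclusion.** The point holds in this form: the 0.01 level is not guaranteed, and the biostatistician's combined roles do not sit with the stated analyst blinding, DMC freedom from competing interests and independent audit.

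The size is conditional. Under between-arm-driven changes and an unadjusted final test, the worst case is about 0.013 to 0.015 two-sided with increases up to double, and at most about 0.028 with unlimited resizing. These are ceilings for the least favourable choice of size, not expected values. If changes use only blinded data, the excess is essentially nil. The role finding rests on reading the biostatistician as a single role across sections.

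Two further inferences are not supported. One is that blinding as a whole fails: blinding of treating clinicians and outcome assessors, and concealment by sealed opaque envelopes, are stated separately and are not in question. The exposure is on the analysis and DMC side. The other is that the interim is mistimed: the trigger can be read in more than one way, and a late look is not an error.

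**What to change.** **Adaptation.** State that interim-driven changes are limited to sample-size re-estimation from pooled, blinded quantities (overall abstinence rate, pooled standard deviation, drop-out), alongside safety review by the DMC. Allow no change based on a between-arm outcome comparison unless a combination or conditional-error test is fixed beforehand.

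**Roles.** Have a DMC member with no other trial role chair the committee, and take the trial biostatistician off it. Keep the allocation list with someone who neither handles nor analyses outcome data. If more than one biostatistician is already intended, name the roles separately.

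**Cost.** Amended protocol and charter wording and reassignment of existing tasks, with no added patients or visits. The sponsor gives up the freedom to redesign on unblinded results.
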